## Methods

### Study design

PePiTA is a prospective, multicenter, non-randomised trial. Patients with histologically confirmed colon adenocarcinoma compatible with clinical stage III are eligible for study screening. The study design is illustrated in Figure 1.

**Figure 1 F1:**
[figure not shown]
Study design.

### Objectives

PePiTA’s primary objective is to examine the ability of PET/CT-assessed tumor FDG uptake after one course of preoperative chemotherapy to predict the outcome of adjuvant therapy, as measured by 3-year DFS among patients with pathological stage III.

Secondary objectives are to examine the predictive value of changes in PET/CT-assessed tumor FDG uptake on OS, to define the best cut-off value of FDG uptake for predicting treatment outcome, and to analyse the cost-effectiveness of such preoperative chemosensitivity testing.

Exploratory (translational research) objectives in the context of several sub-studies are 1) to assess the predictive value of CTCs for DFS, 2) to examine the predictive value of SNPs for DFS with respect to genes related to toxicity or drug targets, 3) to assess genomic rearrangements associated with response or resistance to FOLFOX treatment, 4) to identify an immunologic signature associated with metabolic tumor response to FOLFOX therapy and, finally, 5) to create a bank of frozen tumor and blood samples for future translational research studies.

### Patient selection criteria

### Inclusion criteria

Patients 18 years or older, diagnosed with adenocarcinoma of the colon compatible at endoscopy examination with a stage III cancer (invasion of more than one third of the circumferential colonic lumen) and considered curatively resectable (R0) based on standard preoperative evaluations, are eligible for inclusion.

The patients must have good performance status (WHO performance status 0 or 1), never have received chemotherapy or pelvic irradiation, have signed informed consent prior to any study specific procedures, and have agreed to use effective contraception during the study and until six months thereafter.

### Exclusion criteria

In addition to pregnant or breast-feeding women, excluded from the study are patients identified with any of the following conditions or characteristics: suspected metastatic disease; rectal cancer (located within 15 cm from the anal verge by endoscopy or under the peritoneal reflection at surgery); serious illness like inflammatory bowel disease, central nervous system disease, peripheral neuropathy, clinically relevant coronary artery disease, history of myocardial infarction in the last six weeks, high risk of uncontrolled arrhythmia, or previous malignancy in the last five years (except basal-cell carcinoma of the skin or in situ cervical carcinoma); hypersensitivity to any of the components of study treatments; major surgical procedure, open biopsy or significant traumatic injury within 28 days prior to the study; and having incompletely healed wounds or anticipating the need for major surgery during the course of the study.

### Treatment

All eligible patients will undergo FDG-PET/CT imaging at baseline and then after one cycle of FOLFOX [3] preoperative chemotherapy (a 2-hour infusion of 200 mg/m2 leucovorin or equivalent, followed by a bolus of 400 mg/m2 fluorouracil and then a 22-hour infusion of 600 mg/m2 fluorouracil given on 2 consecutive days; a two-hour infusion of 85 mg/m2 oxaliplatin on day 0, simultaneously with leucovorin, using a Y-infusion device) followed by surgery.

After surgery, patients will be fully evaluable in the study and receive adjuvant FOLFOX when they meet the following criteria: the delay between the first PET/CT scan and the start of neoadjuvant FOLFOX was less than 7 days; the second PET/CT scan was performed on D14 (range: D13-D15); postoperative pathology confirms stage III (pTNM) adenocarcinoma of the colon; and CEA level measured one month after surgery is less than 1.5 × ULN.

All patients, both those meeting the inclusion criteria only and those fully evaluable for the primary objective, will be followed for DFS and OS assessment. Time zero for the assessment of time-to-event outcomes is the first day of pre-operative chemotherapy. In case a patient dies or is lost to follow-up before surgery, he or she will be excluded from the analysis of DFS and OS. The schedule of assessments is described in Figure 2.

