### Follow-up

Follow-up procedures after completion of adjuvant treatment have to follow standard European clinical recommendations for patients with stage II and III colon cancer: every 3 months for the first 2 years and every 6 months for the next 3 years. This includes history and physical examination, serum CEA evaluation, chest X-ray (CT scan upon suspicion of lung metastases), and abdominal ultrasound or CT scan. Clinical follow-up data will be obtained for all patients, including those with stage II disease, with a minimum follow-up time of three years.

Stage IV diseases discovered at baseline FDG-PET/CT or during the surgical intervention deemed to remove the tumor, will not be followed afterwards within the study scheme.

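### Time zero is the first day of preoperative chemotherapy, but deaths and losses before surgery are deleted from DFS and OS and stage IV found at surgery is not followed: all-patient survival is inflated, and the stage III analysis counts guaranteed event-free time

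*Protocol article*

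**What the plan says.** Three rules in the protocol article bear on this point.

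- **Time origin (Treatment).** "Time zero for the assessment of time-to-event outcomes is the first day of pre-operative chemotherapy".
- **Exclusion (Treatment, next sentence).** If a patient "dies or is lost to follow-up before surgery, he or she will be excluded from the analysis of DFS and OS".
- **Stage IV (Follow-up).** Disease found to be stage IV on the baseline scan or "during the surgical intervention deemed to remove the tumor, will not be followed afterwards within the study scheme".

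Against these, Treatment also states: "All patients, both those meeting the inclusion criteria only and those fully evaluable for the primary objective, will be followed for DFS and OS assessment". Follow-up likewise promises clinical data on everyone, stage II included, for at least three years.

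Full evaluability (Treatment) depends on facts known only after time zero: a second scan on D13 to D15, pathological stage III, and a CEA below 1.5 × ULN one month after surgery. Objectives restricts the primary objective to pathological stage III. It places no such restriction on the secondary objective for OS.

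**The concern.** A patient enters the analysis only after satisfying a condition that is met later than the start of the clock. This has two consequences.

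First, in any analysis of all patients, a death between day one of chemotherapy and surgery is an OS event after time zero, and it is removed. A loss in that interval would normally be censored at last contact, and it is removed too. A patient found to be stage IV at surgery has already had chemotherapy and normally both scans, but the later death is never recorded. Survival counted from the start of preoperative treatment then describes only those who came through it.

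Second, everyone in the evaluable stage III set was necessarily alive and under observation until the postoperative CEA. No event in that set can fall in this interval, yet it is counted as time at risk.

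At stake are the absolute 3-year DFS and the all-patient OS and DFS results. The time origin can be corrected at analysis, but follow-up that was never collected may not be recoverable.

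**Working it through.** **1. Reproducing the plan's figures (Statistical considerations).** Non-responder DFS: 0.69^(1/0.63) = 0.555, stated as 55%. Responder DFS at a 50% response rate: 2 × 0.69 − 0.55 = 0.83. Hazard ratio: ln 0.83 / ln 0.55 = 0.312. Schoenfeld events, two-sided 5%, 90% power: 4 × (1.960 + 1.282)² / (ln 0.312)² = 30.9, so 31, against 33 stated; a hazard ratio of 0.32 gives 33. Registration: 135 / 0.60 = 225. The planning figures hold together, and none depends on the rules at issue.

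**2. Guaranteed time in the stage III set.** With a constant hazard and no events possible in the first g years, 3-year DFS becomes 0.69^((3 − g)/3). The documents give no interval to surgery, so g is assumed:

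| g | 3-year DFS |
|---|---|
| 14 days (surgery straight after the second scan) | 69.3% |
| 45 days (D14 plus one month to CEA) | 70.1% |
| 8 weeks | 70.3% |
| 13 weeks | 71.2% |

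Applying the formula to 55% and 83% separately and averaging gives nearly the same: 69.3% at 14 days, 70.0% at 45 days and about 71% at 13 weeks.

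Both log-survivals are multiplied by the same factor (3 − g)/3, so ln S(responder) / ln S(non-responder) stays at 0.312 for every g.

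**3. Deleted failures in all-patient analyses.** Let f be the share of registered patients who are deleted and would have failed by three years. If S is the reported survival, survival with them included is S × (1 − f). The documents give neither f nor an all-patient S. With S = 69% as a stand-in and f assumed:

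| f | patients of 225 | survival with them included |
|---|---|---|
| 1% | 2.3 | 68.3% |
| 2% | 4.5 | 67.6% |
| 3% | 6.8 | 66.9% |
| 5% | 11.3 | 65.6% |

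**4. Direction of any bias in an all-patient PET contrast.** Take 55% and 83% as the reported values and restore deleted failures, as shares of each group (assumed):

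| non-responders / responders | restored survival | ratio of log survival |
|---|---|---|
| none | 55.0% / 83.0% | 0.312 |
| 4% / 0% | 52.8% / 83.0% | 0.292 |
| 4% / 2% | 52.8% / 81.3% | 0.323 |
| 4% / 4% | 52.8% / 79.7% | 0.356 |

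In the first restored case, deletion had understated the contrast. In the other two it had overstated it, even with early failure twice as common in non-responders.

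**The case against.** The strongest reply is that the deletions cannot touch the primary analysis. A patient who dies before surgery has no pathological stage, and one found to be stage IV is not stage III. Neither could be among the 135. This stands. What remains for the primary set is the time origin, and that shift is common to both PET groups.

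Other parts of the defence also stand and rule out stronger readings:

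- A reader might infer bias towards no difference because early failure should be commoner in non-responders. The documents give no such rates, and step 4 shows that the direction can go either way. Patients who die before the second scan have no PET class at all.
- A reader might set the deleted patients against the 33 planned events. Those events belong to the 135 stage III patients; the deleted patients come from the 225 registered.
- A reader might infer that cost-effectiveness and quality-adjusted life expectancy are distorted. The exclusion sentence names only DFS and OS, and the health economic and quality of life sections state no such exclusion.
- A reader might call the result non-comparable with the 69% planning figure. The time origin of that figure is not in the documents, and an adjuvant population has also reached surgery.

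The Follow-up rule can be read as a specific exception to a general sentence. Exclusion of stage IV confirmed after the baseline scan is an eligibility matter, and DFS suits poorly a patient who may never have been disease-free. This narrows the conflict to OS follow-up of stage IV found at surgery, but there it remains. Deleting rather than censoring losses changes little numerically, because these patients would add only short follow-up.

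None of this defends the secondary OS objective, which is not limited to stage III and from which true deaths are removed by rule.

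**Conclusion.** The point holds in limited form and should be fixed. As written, the rules delete failures after time zero from all-patient OS and DFS. Survival there is inflated by a factor of 1/(1 − f), with f unknown: 0.7 to 3.4 points if f is 1 to 5% and reported survival is 69%. Any effect on an all-patient PET contrast has no established direction.

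In the stage III primary set, the defect is a time origin earlier than entry. It adds about 0.3 to 2.2 points to 3-year DFS for 14 days to 13 weeks of guaranteed time under a constant hazard. For fully evaluable patients the CEA condition makes the lower end unlikely. The hazard ratio stays essentially at 0.312, and the 33 events, 135 patients and 225 registrations are unaffected. The documents do not support the stronger conclusion that the primary comparison loses its earliest failures or is biased in a known direction.

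**What to change.** 1. Delete the sentence that excludes deaths and losses before surgery. For all-patient OS and DFS from day one of preoperative chemotherapy, count pre-surgery deaths as events and censor losses at last contact.
2. For all-patient comparisons by PET response, use a landmark at the second PET/CT: start the clock there and count every later death.
3. Keep vital-status follow-up for patients found to be stage IV at surgery, and reconcile the Treatment sentence that all patients "will be followed for DFS and OS assessment" with the Follow-up sentence that these patients "will not be followed afterwards within the study scheme".
4. For the fully evaluable stage III set, keep the population as defined. Either use delayed entry at the date evaluability is established or start the clock on that date, and report which was done beside the 3-year DFS.

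The cost is protocol and analysis-plan wording, plus vital-status follow-up for what are probably few patients. The sample size and the primary population do not change.

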**Figure 2 F2:**
[figure not shown]
Schedule of assessments.

### FDG-PET/CT imaging

Whole body static FDG-PET/CT scans will be performed as described above. The local clinical investigators will be informed about the results of the baseline FDG-PET/CT. In case this scan shows suspicion of stage IV disease, a targeted confirmatory work-up is required before definite exclusion.

The results of the second FDG-PET/CT will be blinded to all local clinical investigators until there is formal documentation of relapse or progression.

Major efforts are undertaken to standardise patient preparation, FDG-PET/CT acquisition, image reconstruction, and semi-quantification of FDG uptake. This is centrally coordinated by the Imaging Core Lab at Institut Jules Bordet’s Nuclear Medicine Department. Strict standardisation will ultimately allow reliable pooling of the FDG-PET/CT imaging data from all participating centres. All participating FDG-PET/CT centres will be required to adhere to the quality assurance guidelines defined by the Belgian Hospital Physicists Association, and to perform a standard phantom (NEMA-type) acquisition, which will ultimately be used for a cross-calibration of all PET cameras.

The response assessment of the primary tumor will be performed according to the European Organisation for the Research and Treatment of Cancer (EORTC) guidelines: a metabolic response corresponds to a ≥15% decrease of the standardised uptake value max. In case of the presence of locoregional lymph node(s) observed on the baseline FDG-PET/CT, a similar response analysis will be performed for each lesion separately.

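### The blind on the second, preoperative PET/CT covers all of its results, which is wider than protecting the SUV-based marker requires and would withhold urgent findings before surgery

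*Protocol article*

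**What the plan says.** All statements are in the Protocol article.

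- **Coverage (FDG-PET/CT imaging).** "Whole body static FDG-PET/CT scans will be performed as described above".
- **Baseline scan (same section).** "The local clinical investigators will be informed about the results of the baseline FDG-PET/CT". It continues: "In case this scan shows suspicion of stage IV disease, a targeted confirmatory work-up is required before definite exclusion".
- **Second scan (same section).** "The results of the second FDG-PET/CT will be blinded to all local clinical investigators until there is formal documentation of relapse or progression".
- **Marker (same section).** For the primary tumor, "a metabolic response corresponds to a ≥15% decrease of the standardised uptake value max". Locoregional nodes seen at baseline get a similar analysis, lesion by lesion.
- **Timing (Treatment).** Among the conditions for full evaluability is that "the second PET/CT scan was performed on D14 (range: D13-D15" in range. Surgery follows this scan.
- **Use of the response (Treatment).** Adjuvant FOLFOX depends on scan timing, pathological stage III and postoperative CEA. Metabolic response is not a condition.
- **Stage IV disease (Follow-up).** Patients whose stage IV disease is found on the baseline PET/CT or at surgery leave study follow-up. The second scan is not named.

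**The concern.** The blind has a sound purpose: treating clinicians should not know whether the tumor responded metabolically, since that could influence management and outcome assessment. The sentence, however, blinds the results as a whole, not the response measurement. A whole-body scan can show things that are not part of the marker, such as a suspected distant lesion or another finding that needs prompt action.

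Followed as written, the clinicians responsible for the patient would not receive such a finding before operating. At stake is the safety of individual patients: a suspicion that triggers a work-up on the first scan has no stated handling when it first appears on a scan about two to three weeks later, just before a resection planned as curative.

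**Working it through.** No figure in the article depends on this point, so the check is mainly a comparison of statements.

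**1. What the word results covers.** Two neighbouring paragraphs of the FDG-PET/CT imaging section use it.

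| | Baseline scan | Second scan |
|---|---|---|
| Coverage | Whole body | Whole body |
| Results given to local clinical investigators | Yes | No |
| Suspected stage IV disease | Confirmatory work-up required | Nothing stated |
| Position | Before chemotherapy | After one cycle, before surgery |

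For the baseline scan the word plainly includes staging findings, because the next sentence says what to do about them. Nothing printed gives it a narrower meaning for the second scan.

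**2. What must be hidden to protect the marker.** The marker is the SUVmax change in the primary tumor, with a parallel analysis of nodes seen at baseline. The items to withhold are therefore the SUV measurements and the response class. Since adjuvant FOLFOX does not depend on response, no treatment rule requires anything further to be hidden.

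**3. Whether the release condition helps.** The blind ends once relapse or progression has been formally recorded. Clinicians who cannot see the scan would have to establish progression by other means. The condition ends the blind; it does not bring the scan's own findings to them before surgery.

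**4. Other checks.** Stage IV disease may be found at the operation (Follow-up), and the Treatment section uses a "CEA level measured one month after surgery". Both come at or after the resection.

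**5. Interval between scans (Treatment).** The baseline scan is less than 7 days before FOLFOX starts. The second is at D13 to D15, counted here from day 0, the day on which the article places oxaliplatin.

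- Shortest: 0 + 13 = 13 days.
- Longest: under 7 + 15 = 22 days.

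**6. Patients covered (Statistical considerations).**

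- Registered: 225.
- Expected pathological stage III: 225 × 0.60 = 135, as the article states.
- Others: 225 − 135 = 90.

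The rule covers at most 225 patients, less any excluded before the second scan. These are patients scanned, not patients with a withheld finding.

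**7. Position relative to time zero (Treatment).** Time zero is the day preoperative chemotherapy starts. The second scan falls 13 to 15 days after it, so removing a patient because of that scan would be a removal after the follow-up clock has started.

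**The case against.** The strongest objection is that this is a one-sentence summary in a condensed article. How a PET/CT centre passes on an urgent finding is ordinary content for a full protocol or imaging manual, and neither is shown. The blind is on local clinical investigators, not on the PET/CT centres or the Imaging Core Lab, so someone can see the images. Because the second scan serves response assessment, its results could be read as meaning the response result. The ethics section also has a general clause favouring patient protection.

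Much of this stands. A reader might infer that the trial orders silence about dangerous findings, or that no safeguard exists; the article supports neither. It does, however, print a positive rule that is too broad, beside a sentence showing that staging findings were considered for the other scan. The readers' access comes with no stated duty to report, and the general clause gives no reporting route or work-up.

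A second objection is that a complete blind is defensible: the second scan is the index test, and anything disclosed from it can change management or become an outcome. This also stands in part. That only the SUV values and response class need hiding is a judgement, and a narrower blind has a cost. If a report cancels or delays resection, the patient may have no postoperative pTNM and drop out of the pathological stage III population. The index scan would then influence who enters the primary analysis, so the narrower blind cannot be called neutral for that comparison.

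Finally, cases are probably few. Suspected metastatic disease is an exclusion, and suspected stage IV on the baseline scan was worked up less than 22 days earlier. That is accepted.

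**Conclusion.** The point holds as a low-cost improvement on patient safety. As printed, the blind reaches further than the tested marker needs and would keep a suspected distant lesion or other urgent finding from the treating team before surgery.

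Its size cannot be stated. Up to 225 patients fall under the rule, but the article gives no rate of new distant or urgent findings at D13 to D15.

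Three stronger readings are not supported:

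- **The two scan rules contradict each other.** They do not; they treat the scans differently, and the second rule is too wide.
- **The DFS comparison is biased by the present rule.** Nothing in the article shows this, and no shift can be computed.
- **The second scan should be unblinded.** The response values should stay hidden.

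The conclusion assumes that the printed sentence reflects the operative rule. If the full protocol or an imaging manual already provides an exception, only the article's wording is at fault.

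**What to change.** In the FDG-PET/CT imaging section:

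1. Limit the blind to the SUV measurements and metabolic-response class of the primary tumor and nodes.
2. Have the existing PET/CT reader report suspected distant disease or other urgent findings on the second scan to the site, with response values removed.
3. Require the same targeted confirmatory work-up as for the baseline scan.
4. Log each release.
5. Keep these patients in DFS and OS follow-up, in line with the Treatment section: "All patients, both those meeting the inclusion criteria only and those fully evaluable for the primary objective, will be followed for DFS and OS". Do not extend to the second scan the rule that ends follow-up for stage IV disease found at baseline or at surgery. Also state how the exclusion of patients who die before surgery applies when a resection is cancelled.
6. Count and report patients whose resection is cancelled or delayed after such a report, including those left without a pTNM.

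**Cost.** Protocol wording and a redacted report from a scan already acquired. No scan is added, and the planned sample size, event count, power and alpha are unchanged. The downsides are that a site may infer non-response in a few patients, that their management before surgery may change, and that some may leave the pathological stage III primary population. How such a patient is then treated is for the sponsor and investigators to decide.
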